**Document Version History**

| Version Date | Version | Author | Signature | Change Description                             | Reason/Comment                                                                                 |
|---------------------|----------------|---------------|------------------|-------------------------------------------------------|-------------------------------------------------------------------------------------------------------|
| December 2023       | 1              | [name]  |                  | Initial release.                                      | Not applicable.                                                                                       |
| 15 January 2024     | 2              | [name]  |                  | Secondary outcomes edited. Sensitivity analysis added | Follow-up questionnaire removed from some outcomes and sensitivity analysis added for primary outcome |
|                     |                |               |                  |                                                       |                                                                                                       |

**LIST OF ABBREVIATIONS**

|          |                                                                   |
|----------|-------------------------------------------------------------------|
| AE       | Adverse Event                                                     |
| BCG      | Bacille Calmette-Guérin                                           |
| CRF      | Case Report Form                                                  |
| DAG      | Directed Acyclic Graph                                            |
| GCP      | Good Clinical Practice                                            |
| ISAAC    | International Study of Asthma and Allergies in Childhood          |
| ITT      | Intent-To-Treat                                                   |
| LAR      | Legally acceptable representative                                 |
| MIS BAIR | The Melbourne Infant Study: BCG for Allergy & Infection Reduction |
| PI       | Principal Investigator                                            |
| PICF     | Participant information and consent form                          |
| SAE      | Serious Adverse Event                                             |
| SAP      | Statistical Analysis Plan                                         |
| SD       | Standard Deviation                                                |
| SE       | Standard Error                                                    |

## 1. STUDY OBJECTIVES

### 1.1. PRIMARY OBJECTIVE

To determine if in healthy neonates (Participants), BCG vaccination in the first ten days of life (Intervention), compared to no BCG vaccination (Comparator), reduces the incidence of 'asthma ever' (Outcome) at five years of age (Time).

### 1.2. SECONDARY OBJECTIVES

To determine if in healthy neonates (Participants), BCG vaccination at birth (Intervention), compared to no BCG vaccination (Comparator) reduces the:

1. incidence of current asthma (Outcome) at five years of age (Time)
2. incidence of current wheeze (Outcome) at five years of age (Time)
3. incidence of severe asthma (Outcome) at five years of age (Time)
4. use of preventer and reliever asthma medication (Outcome) at five years of age (Time)

Note that the MIS BAIR study has other outcomes for allergy, infection and eczema at both one and five years of age. This Statistical Analysis Plan relates only to the asthma outcomes.

## 2. BACKGROUND/INTRODUCTION

### 2.1. STUDY DESIGN

MIS BAIR is a phase III, randomised, controlled trial in infants to determine if the bacille Calmette-Guérin (BCG) vaccine reduces the incidence of eczema, allergies, infections and asthma in the first five years of life.

Infants were recruited at Mercy Hospital for Women, Werribee Mercy, Geelong Hospital, St John of God and Murdoch Children's Research Institute in Melbourne over a three-year period from August 2013 to September 2016. At trial design we planned to randomise 1,438 infants 1:1 to receive the BCG vaccine or no vaccine. However, recruitment to the study was stopped before this number was reached as the BCG-Denmark vaccine became unavailable due to a worldwide shortage. The actual number randomised was 1272. Infants were randomised within ten days of birth.

The study involved two parts:

Part 1 – From birth to one year of age

Part 2 – From one to five years of age

At the 1-year MIS BAIR visit participants were asked to re-consent if they wished to continue into Part 2 of the study. For those families who had not been consented at the 1-year MIS BAIR visit, had not verbally declined participation and had given consent to be contacted for future studies, an invitation letter and the PICF were sent to them by email, post or through REDCap and they could consent by post, on REDCap or in person (e.g. at a study visit). Of the 1272 in Part 1, 1027 consented to continue into Part 2.

### 2.2. INTERVENTION GROUPS

Randomisation was stratified by:

- (i) site (hospital),
- (ii) method of delivery (Caesarean vs non-Caesarean) and
- (iii) plurality of birth (i.e. twins vs singletons).

Neonates were randomised within 10 days of birth to BCG vaccine or no BCG vaccine. Those randomised to BCG vaccine were to receive the vaccine within 24hrs of randomisation (and still within 10 days of birth).

Study participants randomised to group 1 received a single 0.05 mL intradermal dose of BCG-Denmark vaccine SSI (a freeze-dried live vaccine prepared from an attenuated strain of *Mycobacterium bovis*) over the left deltoid, within 10 days of birth. Vaccination could be deferred where the infant was medically unstable, until the infant was in good medical condition as determined by the treating clinician, for a maximum period of 24 hours.

A total of 57 participants were vaccinated with BCG vaccine batch 114010C (expiry 06/2016) after the manufacture assigned used-by-date within three months of expiration (use past the expiry date for the study was approved by the governing HRECs).

At the 1-year and 5-year visits, the member of the research team doing the assessment was blinded to treatment group allocation - they had no access to the randomisation allocation data and a bandage was applied to the upper left infant's arm to hide any potential scar. Parents/guardians of participants could not be blinded to the treatment group allocation due to the localized reaction and scar formation following BCG vaccination.

## 2.3. STUDY POPULATION

1,272 healthy newborns were randomised, within 10 days of birth, in a 1:1 ratio, to study group 1 (BCG, n=637) or study group 2 (no BCG, n=635). Twin pairs were randomised to the same group but only one twin from each pair was included as a study participant, regardless of birth order. A total of 21 sets of twins were randomised in the trial and 17 sets of twins continued into Part 2.

### 2.3.1. Inclusion Criteria

For MIS BAIR (Part 1):

- Less than 10 days old;
- English speaking mother;
- An informed consent form must be signed and dated by their parent(s) or legally acceptable representative (LAR) after the nature of the study has been explained and prior to any study assessments/procedures;
- The infant's mother has screened negative for HIV during this pregnancy;
  - To ensure this is accurate, before randomisation staff will check the mother's pathology results to confirm the date of her HIV test is post conception for the current pregnancy (this date is recorded on the eligibility check form)
- Born no earlier than eight weeks before estimated date of delivery;
- Birth weight >1500g;
- The LAR expects to be able to complete four online/phone questionnaires over the infant's first 12 months of life and for the infant to be available for skin prick testing at a study site at 1-year of age.

Additional inclusion criteria for part 2:

- Were randomised in part 1 of MIS BAIR

### 2.3.2. Exclusion Criteria

For MIS BAIR (Part 1):

An infant meeting any of the following criteria will be excluded from study participation (as per the NH&MRC Immunisation Handbook (10th edition, 2013)):

- Any indication for BCG immunisation in the first 12 months of life including:
  - likely travel to a high TB incidence country in the first year of life;
  - aboriginal and Torres Strait Islander babies living in parts of Australia where the incidence of TB is higher;
  - newborn babies, if either parent has leprosy or a family history of leprosy
  - newborn in contact with a patient with TB.
- Known or suspected HIV infection;
- Treatment with corticosteroids or other immunosuppressive therapy, including monoclonal antibodies against tumour necrosis factor-alpha (TNF-alpha) (e.g. infliximab, etanercept, adalimumab);
- Born to a mother treated with bDMARDs (e.g. TNF-alpha blocking monoclonal antibodies) in the 3rd trimester;
- Congenital cellular immunodeficiencies including specific deficiencies of the interferon gamma pathway;
- Malignancies involving bone marrow or lymphoid systems;
- Serious underlying illness including severe malnutrition;
- Medically unstable;
- Generalised septic skin disease and skin conditions such as eczema, dermatitis and psoriasis;
- Significant febrile illness;
- Sibling in the study (other than a twin)
- Multiple births more than twins.
- Born to mother who has tested Hep B antigen positive in current pregnancy and whose baby is likely to be given hepatitis B immunoglobulin.
- Mother has received celestone/betamethasone 48 hours before randomisation

Also excluded are infants with:

- a mother who is immunosuppressed;
- a family history of immunodeficiency;
- consanguineous parents.

Additional exclusion criteria for part 2:

- Excluded during Part 1 of the study
- Withdrawn during Part 1 of the study

### 2.4. SAMPLE SIZE

The original sample size estimate (n=1438) was calculated for outcomes at the 1-year timepoint, rather than for the asthma outcomes. The sample size was calculated based on a 'worse case scenario' assumption that complete 1-year data would only be available for 80% of participants, i.e. 1,150. This sample size was powered to detect a 35% or greater reduction in skin prick test

The Asthma in Australia 2011 report, indicated that for children 4-5 years of age 15.4% have 'current asthma' defined as 'ever told by a doctor they have asthma' AND 'yes' to 'In the last 12 months, has the child had an illness with wheezing in the chest which lasted for a week or more or taken any medication for asthma?' and 22% have 'asthma ever' defined as 'ever been told by doctor that their child has asthma'. Assuming that 90% of participants would remain in the study to 5 years (n=1294), it was estimated that this sample size would allow detection of an absolute reduction in current asthma of 5.5% (15% to 9.5%) and an absolute reduction in 'asthma ever' of 6% (22% to 16%).

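### SAP section 2.4 still gives the asthma outcomes' detectable reductions for 1294 children at 5 years, although 1272 were randomised and 1027 entered Part 2; no figure is given for the achieved numbers.

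*SAP*

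**What the plan says.** Section 2.4 explains that "The original sample size estimate (n=1438) was calculated for outcomes at the 1-year timepoint, rather than for the asthma outcomes". It then turns to 5 years: "Assuming that 90% of participants would remain in the study to 5 years (n=1294), it was estimated that this sample size would allow detection" of two effects. For the primary outcome it is "an absolute reduction in 'asthma ever' of 6% (22% to 16"%). For the first secondary outcome it is "detection of an absolute reduction in current asthma of 5.5% (15% to 9.5"%). No significance level or power is given for either effect in the text at hand.

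Section 2.1 reports that recruitment ended early because of the vaccine shortage: "The actual number randomised was 1272". Section 2.3 gives the allocation as "in a 1:1 ratio, to study group 1 (BCG, n=637) or study group 2 (no BCG, n=635"). Section 2.1 also reports the step into the later follow-up: "Of the 1272 in Part 1, 1027 consented to continue into Part 2".

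The version history dates the SAP to December 2023, with a revision in January 2024. Both counts were known by then.

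**The concern.** The detectable reductions assume 22 more children than were randomised (1294 − 1272) and 267 more than entered Part 2 (1294 − 1027). The assumed 90% retention to 5 years had already failed at the Part 2 consent step, before any later loss. The SAP reports these counts but does not carry them into section 2.4. The superseded figures are therefore the only guide to the trial's sensitivity for asthma.

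What is at stake is how a null result is read. Someone who takes section 2.4 at face value may think a 6-point reduction would very probably have been found, and so read an inconclusive result as evidence of no effect.

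**Working it through.** **Inputs from the SAP.** Planned 1438, retention 90%, N = 1294, and effects 22% vs 16% and 15% vs 9.5% (section 2.4); 1272 randomised and 1027 in Part 2 (section 2.1); 1:1 allocation (section 2.3).

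**Assumptions.** Two-sided 5%, in line with the 95% intervals in section 5.1; 80% power for detectable differences; equal arms, since the split of the 1027 is not given.

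**The plan's own number.** 0.90 × 1438 = 1294.2, so 1294 reproduces. Achieved consent to Part 2 is 1027 / 1272 = 80.7%.

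**Power.** With n per arm, d = p1 − p2 and p̄ the mean of the two rates:

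power = Φ{[d − 1.96·√(2p̄(1 − p̄)/n)] / √([p1(1 − p1) + p2(1 − p2)]/n)}

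For asthma ever, p̄ = 0.19, 2p̄(1 − p̄) = 0.3078 and p1(1 − p1) + p2(1 − p2) = 0.1716 + 0.1344 = 0.3060.

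- n = 647: (0.06 − 1.96 × 0.02181) / 0.02175 = 0.793, power 0.786.
- n = 513.5: (0.06 − 1.96 × 0.02448) / 0.02441 = 0.492, power 0.689.

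The same formula for current asthma, and solving it for d at 80% power, gives:

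| Total N | Power, 22% vs 16% | 80%-power reduction from 22% | Power, 15% vs 9.5% | 80%-power reduction from 15% |
|---|---|---|---|---|
| 1294 (plan) | 0.7862 | 6.10 points | 0.8557 | 5.13 points |
| 1272 (randomised) | 0.7793 | 6.15 | 0.8497 | 5.18 |
| 1145 (90% of 1272) | 0.7355 | 6.46 | 0.8109 | 5.43 |
| 1027 (Part 2) | 0.6887 | 6.80 | 0.7675 | 5.71 |
| 924 (90% of 1027, an assumption) | 0.6427 | 7.14 | 0.7230 | 5.98 |

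Even at 1294 the two stated effects do not share one power (79% and 86%). At two-sided 5%, exactly 80% for asthma ever would need 1340 children.

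**Where the loss arises.** For asthma ever the total fall is 0.7862 − 0.6887 = 0.0975. Going from 1294 to 1272 costs 0.7 points; going from 1272 to 1027 costs 9.1. The loss therefore arises almost entirely at Part 2 consent. That second step includes the 10% attrition already planned for. Comparing like with like through 1145, early closure accounts for 5.1 points and the retention shortfall for 4.7.

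**Precision.** The 95% half-width for the primary risk difference is 1.96·√(0.3060/n). At n = 647 it is 1.96 × 0.02175 = 4.3 points; at n = 513.5 it is 1.96 × 0.02441 = 4.8 points.

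**Other conventions.** From 1294 to 1027, power for asthma ever falls from 86.6% to 79.1% one-sided, and from 76.5% to 66.0% with continuity correction. The size of the fall does not depend on the convention.

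**The case against.** The strongest reply is that section 2.4 is history. It speaks of an original estimate, says the sample was sized for 1-year outcomes and cites the published protocol, while section 2.1 openly reports the shortfall. That stands: 1294 is neither a miscalculation nor a contradiction. What remains is that the consequence of the shortfall is stated nowhere in a plan written after it was known.

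No defined target was missed, because no alpha or power is attached to the asthma effects. That also stands, and the figures above rest on assumed values. One sentence of section 2.4 about the 1-year outcome breaks off in the text at hand, so a general alpha or power may have stood there.

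The 1027 is not necessarily the number of observed primary outcomes. It caps 5-year questionnaire respondents, but sections 4.2 and 4.3 also accept a no on the 7–10-year questionnaire as a negative for asthma ever and for current asthma. The SAP does not say whether children outside Part 2 were sent it. Such answers could raise the count, while unanswered 5-year questionnaires would lower it. Section 5.3 drops the 7–10-year data in its sensitivity analysis, so the cap applies in full there.

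The primary analysis imputes for all 1272. Imputation recovers only what the auxiliary variables carry and does not restore the power of 1272 observed outcomes.

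Finally, the risk difference will be reported with its 95% interval, and section 5.2.1 will show non-consent and respondents by arm. This limits the harm. It does not correct the sensitivity statement.

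**Conclusion.** The point holds as an un-updated planning statement of moderate size. With two-sided 5% and the SAP's own rates, 1027 children give about 69% power for 22% vs 16% (79% at 1294) and about 77% for 15% vs 9.5% (86% at 1294). The 80%-power reductions are about 6.8 points (6.1 at 1294) and 5.7 points (5.1 at 1294). The expected half-width for the primary risk difference grows from 4.3 to 4.8 points.

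A reader might infer three stronger things that the SAP does not support:

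- That the trial cannot detect a 6-point reduction. Power of about 69% is reduced, not absent.
- That 1294 exceeding 1272 is itself the damage. That gap costs less than one point of power.
- That the figures fail because the planning rates use a doctor-told definition while the primary outcome is the parent's answer to the ISAAC question. The SAP gives nothing from which to size that difference, and restating N would not address it.

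**What to change.** In section 2.4:

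- Label the 22% to 16% and 15% to 9.5% effects as original planning figures for 1294 children, and state the alpha and power assumed.
- Add the detectable differences, or the expected half-width of the interval, for the achieved numbers. Use 1027 as the cap on 5-year questionnaire respondents: about 6.8 and 5.7 points at 80% power, and a half-width of about 4.8 points for the primary risk difference.
- Update these with the blinded, pooled count of observed primary outcomes, including 7–10-year no answers, once it is available.
- State that a null result will be interpreted from the 95% confidence interval.

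The cost is a few sentences and a less favourable stated sensitivity. No estimate or analysis changes and no patients are added.

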## 2.5. STUDY PROCEDURE

**Part 1 MIS BAIR**

BCG (n=637)  
No BCG (n=635)

1-year visit  
blood sample

7d blood sample

Q

3m 6m 9m 12m

**Part 2 MIS BAIR**

AS = Asthma questions IN = Infection questions AL = Allergy questions EC = Eczema questions

Q

18m 24m 30m 36m 42m 48m 54m 60m

cv examination  
dental exam  
blood sample  
food challenge  
skin prick test  
5-year-old visit

87m

An intention-to-treat (ITT) analysis will be used to analyse the outcomes, with all participants analysed according to the study group to which they were randomised, regardless of the intervention they actually received. The only participants excluded from analysis will be participants who withdrew consent for their data to be used.

#### 4. OUTCOME VARIABLES

#### 4.1.1. Questionnaires

(FORM-STAT-04A-01/Version 1.0)

These questionnaires collected data relevant to all the outcomes of the study including skin condition, reactions to allergens, episodes of illness, wheeze/asthma, and vaccinations. This SAP only outlines data collected that is relevant to the asthma outcomes.

#### 4.1.2. ISAAC questions at five years of age

At five years of age the questionnaires included validated questions from the International Study of Asthma and Allergies in Childhood (ISAAC).

These questions are:

1. *Has your child ever had wheezing or whistling in the chest at any time in the past?*  
*Yes/No/Don't know*

If they answer yes to the first question, the following question was asked:

2. *Has your child had wheezing or whistling in the chest in the past 12 months?*  
*Yes/No/Don't know*

If they answer yes to this question, the following questions were asked:

3. *How many attacks of wheezing has your child had in the past 12 months?*  
*None | 1 to 3 | 4 to 12 | More than 12*
4. *In the past 12 months, how often, on average, has your child's sleep been disturbed due to wheezing?*  
*Never woken with wheezing | Less than one night per week | One or more nights per week*
5. *In the past 12 months, has wheezing ever been severe enough to limit your child's speech to only one or two words at a time between breaths?*  
*Yes/No*

All participants were asked:

6. *Has your child ever had asthma?*  
*Yes/No/Don't know*
7. *In the past 12 months, has your child's chest sounded wheezy during or after exercise?*  
*Yes/No*
8. *In the past 12 months, has your child had a dry cough at night, apart from a cough associated with a cold or chest infection?*  
*Yes/No*

#### 4.1.3. Follow-up questionnaire for missing data

At seven to ten years of age parents/guardians of participants were asked to complete a follow-up questionnaire. The purpose of the questionnaire was to identify participants who had *not* had the outcome of interest. The questionnaire was only sent to participants who were known to have

missing data due to not completing all the questionnaires. Only 'no' responses will be taken as valid data.

For asthma, the question asked of participants was:

*Has [child's name] ever had asthma? Yes/No/Unsure*

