## 4.2. PRIMARY OUTCOME

### 1. Asthma ever, defined by ISAAC questions

**Positive** if the parent/guardian answered 'yes' to 'Has your child ever had asthma?' (ISAAC Q6).

**Negative** if the parent/guardian answered

- 'no' to 'Has your child ever had asthma' in the 5-year questionnaire (ISAAC Q6).
- OR
- 'no' to the asthma question in the 7 – 10-year follow-up questionnaire

**Missing** if in the 5-year questionnaire the response to ISAAC Q6 is missing or don't know AND the response to the follow-up questionnaire is not 'no'.

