#### 4.3. SECONDARY OUTCOMES

##### 1. Current asthma at five years of age, defined by ISAAC questions

**Positive** if in the 5-year questionnaire the parent/guardian answered 'yes' to 'Has your child ever had wheezing or whistling in the chest in the chest at any time in the past?' (ISAAC Q1) AND 'Has your child had wheezing or whistling in the chest in the past 12 months?' (ISAAC Q2) AND 'Has your child ever had asthma?' (ISAAC Q6).

**Negative** if in the 5-year questionnaire the parent/guardian answered:

- 'no' to 'Has your child ever had wheezing or whistling in the chest in the chest at any time in the past?' (ISAAC Q1)

OR

- 'yes' to 'Has your child ever had wheezing or whistling in the chest in the chest at any time in the past?' (ISAAC Q1) AND 'no' to either or both of:
  - 'Has your child had wheezing or whistling in the chest in the past 12 months?' (ISAAC Q2)
  - 'Has your child ever had asthma?' (ISAAC Q6) in the five-year questionnaire.

OR

- 'no' to the asthma question in the follow-up questionnaire

**Missing** if in the 5-year questionnaire responses to the above questions are missing AND the response the follow-up questionnaire is not 'no'

OR

The participant does not fulfil the 'positive' or 'negative' criteria above.

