### **5.3. PRIMARY DATA ANALYSES**

The percentage of 'asthma ever' reported at five years will be presented separately for children in the treatment and non-treatment groups. Comparison between the treatment arms will be estimated using binary regression adjusted for the randomisation stratification factor of birth mode. Results will be presented as adjusted risk difference and its 95% confidence interval (CI). The analysis will be presented as ITT with multiple imputation as described above.

The two other stratification factors used for randomisation (site and plurality) will not be included in adjustments because it is already known from Part 1 that 98.3% of infants were singleton and 95.2% were from the same site .

As a sensitivity analysis, the same binary regression model will be re-run excluding the 7-10 year follow-up questionnaire data.

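### A follow-up 'no' at 7-10 years fills a missing primary outcome but a 'yes' leaves it missing, so observation depends on the outcome; the size of the bias is conditional

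*SAP*

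**What the plan says.** Section 4.1.3 describes a questionnaire completed at seven to ten years of age. "The purpose of the questionnaire was to identify participants who had *not* had the outcome of interest". On who received it: "The questionnaire was only sent to participants who were known to have" gaps, namely "missing data due to not completing all the questionnaires". On its use: "Only 'no' responses will be taken as valid data".

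Section 4.2 (primary outcome, asthma ever) lists two routes to a negative: 'no' to ISAAC Q6 at five years, or "no' to the asthma question in the 7 – 10-year follow-up questionnaire". A child stays unclassified when "in the 5-year questionnaire the response to ISAAC Q6 is missing or don't know AND the response to the follow-up questionnaire is not 'no". A follow-up 'yes' or 'unsure' therefore changes nothing.

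Section 4.3 (secondary outcome 1, current asthma) has the same route to a negative: "no' to the asthma question in the follow-up questionnaire".

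Two other parts of the plan bear on this.
- Section 5.2.3 imputes missing outcomes by chained equations. A follow-up 'yes' or 'no' feeds one candidate predictor, 'Evidence of asthma'. The predictors are optional and ranked by priority, and this one is 14th of 16.
- Section 5.3 adds: "As a sensitivity analysis, the same binary regression model will be re-run excluding the 7-10 year follow-up questionnaire data".

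**The concern.** Among children without a usable 5-year answer, the follow-up can turn those without asthma into observed negatives. It can never turn those with asthma into observed positives. Each 'no' is sound for the child concerned, because never having had asthma by seven to ten implies none by five. As a selection rule it is not neutral: the observed data gain non-cases only, and the cases stay in the pool to be imputed.

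Standard chained-equation imputation assumes that, given the variables in the model, missingness does not depend on the unseen value. Here a rule in the plan makes it depend on that value. At stake are the reported percentages in each arm and, to a lesser degree, the primary risk difference.

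Section 2.2 says parents could not be blinded. Follow-up response could therefore differ by arm, and each arm would then gain a different share of added negatives. The SAP does not show that it does differ.

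There is also a gap in the definitions. The form went to families with any incomplete questionnaire, so a child can have Q6 'yes' at five and 'no' at follow-up. That child meets both Positive and Negative in section 4.2. The same overlap exists for current asthma in section 4.3. No rule says which answer prevails.

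**Working it through.** **The plan's own figure.** Section 2.4 assumes 90% retention: 1438 × 0.90 = 1294. It says this allows detection of 22% vs 16% in asthma ever. With 647 per arm and a two-sided 5% test (assumed, not stated), power is 78.6%, so the figure is coherent. The 22% and 16% serve below as true rates.

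**Inputs the SAP does not give (assumed).** 5-year response r = 60-80% of those randomised; follow-up response among the rest q = 20-50%; onset after five in d = 3% of children free of asthma at five; 5-year response unrelated to asthma.

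**Observed rate under the 'no'-only rule.** For true rate p:

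observed = p·r / [r + (1−r)·q·(1−p)·(1−d)]

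With r = 0.70 and q = 0.35:
- Control: 0.154 / (0.70 + 0.30 × 0.35 × 0.78 × 0.97) = 0.154 / 0.7794 = 19.8%.
- BCG: 0.112 / (0.70 + 0.30 × 0.35 × 0.84 × 0.97) = 0.112 / 0.7856 = 14.3%.
- Risk difference: −5.5 points instead of −6.0.

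| r | q | Control (true 22%) | BCG (true 16%) | Risk difference (true −6.0) |
|---|---|---|---|---|
| 0.60 | 0.20 | 20.0% | 14.4% | −5.5 |
| 0.60 | 0.50 | 17.6% | 12.6% | −5.0 |
| 0.80 | 0.20 | 21.2% | 15.4% | −5.8 |
| 0.80 | 0.50 | 20.1% | 14.5% | −5.6 |

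The control rate is 0.8 to 4.4 points low. Imputation without a predictor that carries the follow-up answer reproduces these figures.

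**Unequal follow-up response, no true effect (22% in both arms).** With q of 20% in control and 40% in BCG, the spurious difference is −1.7 points at r = 0.60 (20.0% vs 18.3%) and −0.7 at r = 0.80. With 30% vs 50% it is −1.5 and −0.7.

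**With 'Evidence of asthma' in the imputation.** Large simulated samples, 5% later onset. The predictor is either moderate (sensitivity 0.70, false positives 0.10) or strong (0.90 and 0.03):

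| r | q | Without it | Moderate | Strong |
|---|---|---|---|---|
| 0.65 | 0.60 | 17.8 / 12.8% | 20.5 / 14.9% | 22.1 / 16.1% |
| 0.75 | 0.40 | 19.9 / 14.4% | 21.3 / 15.4% | 22.1 / 16.0% |
| 0.85 | 0.40 | 21.0 / 15.1% | 21.7 / 15.6% | 22.0 / 16.0% |

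With the predictor, the risk difference in these rows lies between 5.7 and 6.1 points in size. A separate simulation under the first set of assumptions (3% onset) left rates 0.3-1.7 points low, and a spurious difference of about 0.3-0.6 points when follow-up response was unequal.

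**Why the moderate predictor repairs only part.** The variable pools a follow-up 'yes' with symptoms at 36 or 48 months. A child with Q6 missing and a follow-up 'yes' never has an observed outcome, so that child's probability is learned from the pooled group. At 22% prevalence, symptoms of moderate quality imply 0.22 × 0.70 / (0.22 × 0.70 + 0.78 × 0.10) = 0.154 / 0.232 = 66% asthma. A follow-up 'yes' alone would imply 0.22 / (0.22 + 0.78 × 0.03) = 90% with 3% later onset, or 85% with 5%.

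**If 5-year response depends on asthma.** Suppose affected families answer more often (80% vs 65%, q = 0.35, d = 3%). Before imputation, Q6 alone reads 0.176 / (0.176 + 0.507) = 25.8%. The current rule reads 0.176 / (0.683 + 0.0927) = 22.7%. If affected families answer less often (65% vs 80%), Q6 alone reads 18.6% and the current rule 17.4%.

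**The case against.** - **The rule has a reason.** A 'no' at seven to ten settles the matter at five, while a 'yes' cannot be dated to before five. This stands as the reason 'yes' is not counted. It does not make the selection neutral.
- **'Yes' answers are not thrown away.** A reader might infer that they are. Section 5.2.3 feeds them into 'Evidence of asthma', and if that variable predicts strongly the bias all but disappears. This stands, except that the variable's inclusion is optional and it comes near the end of the priority list.
- **The effect will be visible.** Section 5.3 already plans an analysis without the follow-up data. True, but the headline estimate keeps the one-sided rule.
- **The inputs may be generous.** If the form went only to the 1027 of 1272 (80.7%) who consented to Part 2, which section 4.1.3 does not say, q cannot exceed (0.807 − 0.70) / 0.30 = 0.36 at r = 0.70, or 0.04 at r = 0.80. With 20-50% of reachable families answering and no auxiliary, the risk difference is −5.7 to −5.9 at r = 0.70 and −5.4 to −5.8 at r = 0.60. The standard error with all 1272 observed is √(0.22 × 0.78 / 635 + 0.16 × 0.84 / 637) = 2.2 points, so the bias in the difference is small beside sampling error. This stands.
- **Q6 alone is not unbiased by construction.** It recovers 22% and 16% only when response is unrelated to asthma given the imputation variables. In the case above where affected families answer more, the current rule lies closer to the truth. This stands as a limit on the remedy.

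**Conclusion.** The mechanism is certain from sections 4.1.3 and 4.2: whether the outcome is observed depends on the outcome, through a rule the plan sets itself. The same applies to current asthma. The missing precedence rule is also plain from the text.

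The size is conditional. If 5-year response is otherwise unrelated to asthma, and under the assumed rates, the control percentage is about 1-4 points low without a predictive auxiliary. It is about 0-2 points low, with little bias in the risk difference, if 'Evidence of asthma' is in the imputation and predicts at least moderately well. With equal follow-up response in the two arms, the difference is mildly attenuated.

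Two stronger readings are not supported. One is that the reported rates must be too low and the effect must be diluted. That ignores the auxiliary variable, and response related to asthma could shift the rates in the other direction. The other is that unblinded parents will produce a spurious benefit. Unequal follow-up response is possible, but nothing in the SAP shows it.

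This should be fixed before unblinding. It does not by itself invalidate the primary analysis.

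**What to change.** Amend the SAP before the data are unblinded (section 5.1 ties full unblinding to final SAPs):

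1. Define the primary outcome by ISAAC Q6 at five years alone. A missing or don't-know answer is imputed.
2. Use the follow-up yes/no answer only as an imputation variable and make it mandatory. Keep it separate from the 36- and 48-month symptoms where the model allows.
3. Move the 'no'-only rule to a sensitivity analysis.
4. Add a sensitivity analysis that counts both 'yes' and 'no' when Q6 is missing. It is not in the current plan. Note that it slightly over-counts because of onset after five (22.0-22.9% against a true 22% in the scenarios run).
5. Treat the 'no' rule for current asthma in section 4.3 the same way.
6. State that a 5-year answer always takes precedence over the follow-up.
7. For each analysis, state whether it is imputed and whether follow-up answers stay in the imputation variables. Section 5.3 does not say this for the planned sensitivity analysis.

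**Cost.** SAP wording and one additional analysis. Some negatives now observed directly would be imputed instead, with a small loss of precision, and some of those children could be imputed as positive. The 5-year-only analysis still assumes that response is unrelated to asthma given the imputation variables, and the report should say so.
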